### 3. OBJECTIVES

As we described previously, within the population of patients with bronchiectasis, colonization with *P. aeruginosa* is associated with increased sputum production, more extensive bronchiectasis on HR-CT of the thorax, more hospitalizations and reduced quality of life. In current guidelines non-CF bronchiectasis patients colonized with *P. aeruginosa* need to be treated with antibiotics, for example nebulized tobramycin. Occasionally, other organisms as well as mixed infections result in similar problems, and these patients may also benefit from inhaled tobramycin.

The objective of this study is to document pharmacokinetics and local tolerability of dry powder tobramycin inhaled by patients with non-CF bronchiectasis by administering 4 different doses of tobramycin: 30, 60, 120 and 240 mg.

#### **Primary objectives**

To establish both pharmacokinetics and local tolerability of DP tobramycin using the Cyclops, in the target population.

#### **4. STUDY DESIGN**

The study will be a single centre, single ascending, single dose study of inhaled dry powder tobramycin as a first step to investigate the pharmacokinetics of four doses with no more local intolerability than when tobramycin is administered by nebulisation. The study includes 8 patients with non-CF bronchiectasis who meet the in- and exclusion criteria. These 8 patients will be recruited from the outpatient department of pulmonology.

See tables 1 and 2 for interventions and a timetable

**Table 1 Study procedures**

|               | Procedure                                                           | Extra for study | Invasive | For study objective |
|---------------|---------------------------------------------------------------------|-----------------|----------|---------------------|
| Medication    | Study medication                                                    | X               | N        | primary             |
| Measurements  | Inhalation instruction                                              | X               | N        | primary             |
|               | Inhalation flow measurement                                         | X               | N        | primary             |
|               | Serum levels                                                        | X               | Y        | primary             |
|               | Serum creatinin                                                     | X               | Y        | primary             |
|               | Lung function                                                       | X               | N        | primary             |
|               | X-ray of the chest, if not performed the last year before screening | X               | N        | primary             |
| Medical check | Routine check up                                                    | X               | N        |                     |

**Table 2. Timetable of the study**

| Visit | Time table          | Time needed | Procedure                                                                                                                                                                                                                                                                                                        |
|-------|---------------------|-------------|------------------------------------------------------------------------------------------------------------------------------------------------------------------------------------------------------------------------------------------------------------------------------------------------------------------|
| 1     | Day 1               | 15 minutes  | Explanation study design and invitation to participate in the study                                                                                                                                                                                                                                              |
| 2     | Day 15              | 30 minutes  | Informed consent
Routine medical check, including spirometry and if necessary a X-ray of the chest                                                                                                                                                                                                            |
| 3     | Day                 | 13 hours    | Inhalation instruction
Medication inhalation, 1 st dose = 30 mg
Inhalation flow measurement
Collecting inhalation device
Measuring amount of tobramycin remaining in the device
Serum samples collection – from indwelling venous catheter
Spirometry
Scoring of adverse effects |
| 4     | Day 7 after visit 3 | 13 hours    | Inhalation instruction
Medication inhalation, 2nd dose = 60 mg
Inhalation flow measurement
Collecting inhalation device
Measuring amount of tobramycin remaining in the device
Serum samples collection – from indwelling venous catheter
Spirometry
Scoring of adverse effects             |
| 5     | Day 7 after visit 4 | 13 hours    | Inhalation instruction
Medication inhalation, 3rd dose = 120 mg
Inhalation flow measurement
Collecting inhalation device
Measuring amount of tobramycin remaining in the device
Serum samples collection – from indwelling venous catheter
Spirometry
Scoring of adverse effects            |
| 6     | Day 7 after visit 5 | 13 hours    | Inhalation instruction
Medication inhalation, 4th dose = 240 mg
Inhalation flow measurement
Collecting inhalation device
Measuring amount of tobramycin remaining in the device
Serum samples collection – from indwelling venous catheter
Spirometry
Scoring of adverse effects            |

## 5. STUDY POPULATION

### 5.1 Population (base)

All participants will be patients with non-CF bronchiectasis and will be recruited via the outdoor department of the department of pulmonary diseases of the UMCG. Due to the low number of study participants needed to perform this study we expect to reach the target number of patients needed for this study within several months.

### 5.2 Inclusion criteria

- Age 18 years or older
- Obtained informed consent
- Patients having bronchiectasis (confirmed with HR-CT of the chest)

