## SUMMARY

**Rationale:** Bronchiectasis is a persistent and frequently progressive condition characterized by dilated and thick-walled bronchi retaining sputum. There are multiple underlying causes, of which cystic fibrosis (CF) is the best known, but frequently no cause can be identified. The main symptoms of bronchiectasis are cough and chronic sputum production. There is a state of constant colonization with bacteria, which frequently causes exacerbations. The presence of *Pseudomonas aeruginosa* is an unfavorable prognostic indicator and is associated with increased sputum production, more extensive bronchiectasis on HR-CT of the thorax, more hospitalizations and reduced quality of life. Until now, most patients with non-CF bronchiectasis who are colonized with *P. aeruginosa* receive inhaled tobramycin every other month, by use of a nebulizer. However, this delivery system has several disadvantages, like a low lung deposition and pollution with tobramycin in the surrounding environment. With an efficient dry powder inhaler (DPI), a three to six fold higher lung deposition compared to a nebulizer can be obtained. Therapy with a DPI is also less time consuming compared to nebulisation. Nebulised tobramycin is used most in routine care; there is also one, rather poorly characterized DPI for tobramycin available, though this DPI is not registered for non-CF bronchiectasis. We will investigate dry powder tobramycin (DP tobramycin) in a novel device in patients with non-CF bronchiectasis colonized with *P. aeruginosa*.

**Objective:** The main objectives are to investigate the pharmacokinetic properties of DP tobramycin at different dosages together with the local tolerability of DP tobramycin via the Cyclops® at different dosages.

**Study design:** single center, single ascending, single dose, response study.

**Study population:** 8 patients with non-CF bronchiectasis

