### 5.3 Exclusion criteria

- Pregnant or breast feeding
- Subjects with known or suspected renal, auditory, vestibular or neuromuscular dysfunction, or with severe, active haemoptysis,
- History of adverse events on previous tobramycin or other aminoglycoside use
- No concurrent use of cyclosporin, cisplatin, amfotericin B, cephalosporins, polymyxins, vancomycin and NSAIDs.

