#### **6.6.1. Dosages:**

We will do an ascending dose response study with 4 different doses (30, 60, 120 and 240 mg). The doses will be fixed rising to react to possible adverse events and a possible end of the study for the participant.

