### 9.2 Inferential statistics

Univariate analysis will be used to test if co-variables, including sex, ethnicity, co-morbidity, medical history, dose and duration of (TB) and co medication have an effect on PK parameters like  $T_{max}$ ,  $C_{max}$  and the (unbound)  $AUC_{0-24h}$  of tobramycin. Differences in clinical parameters between baseline and end of study will be calculated. When not normally distributed, non-parametric tests were used, i.e. Mann-Whitney  $U$  test and Wilcoxon rank sum test for ordinal data and Chi square tests will be used for nominal data. Correlation coefficients (Spearman's or Pearson's depending on distribution) will be used to test

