### g. Study population

Patients with non-CF bronchiectasis, with recurrent bacterial exacerbations (i.e.,  $\geq 2$  in previous year) – with or without *Pseudomonas aeruginosa* isolated from sputum.

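### No stable-disease requirement: with doses rising weekly in every patient, cough or dyspnoea from an exacerbation can be counted as an effect of that day's dose

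*Protocol*

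**What the plan says.** **Entry.** Section 5.2 lists age, consent and "Patients having bronchiectasis (confirmed with HR-CT of the chest". Section 5.3 covers pregnancy and breast feeding, organ dysfunction, severe haemoptysis, "History of adverse events on previous tobramycin or other aminoglycoside use" and a list of co-medications. Neither list mentions stable disease or a recent exacerbation. Section 12.1.g gives a narrower population: "Patients with non-CF bronchiectasis, with recurrent bacterial exacerbations", defined there as two or more in the previous year. The Summary says of the disease: "There is a state of constant colonization with bacteria, which frequently causes exacerbations".

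**Schedule.** Table 2 sets the second dose at "Day 7 after visit 3" and the fourth at "Day 7 after visit 5", with no visit window and no provision for an exacerbation in between. Section 6.6.1 explains the order: "The doses will be fixed rising to react to possible adverse events". Section 7.2 marks randomisation as not applicable.

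**Tolerability.** This is a primary objective. The Summary bases it on scored adverse events, cough above all, and on lung function. Section 8.2.1 records adverse events regardless of relation to the product. Section 9.1 reports the proportion of subjects with adverse effects on treatment days. Section 7.3.7 schedules spirometry just before each inhalation and at 15, 30 and 90 minutes after it. Section 9.2 adds: "Differences in clinical parameters between baseline and end of study will be calculated".

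**The concern.** Dose and calendar time are the same variable here: 30 mg is always week 0 and 240 mg is always week 3. Comparing doses within a patient then relies on the disease staying put between visits 3 and 6, and the protocol neither requires nor records that it does.

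Cough is both a leading symptom of bronchiectasis and the adverse event of most interest. A patient who enters while recovering from an exacerbation may cough less as the dose rises. One who exacerbates later may cough more at 120 or 240 mg. With no symptom record before dosing and no relatedness filter on the count, the per-dose proportion cannot tell either course from a drug effect. The baseline-to-end comparison in 9.2 spans the whole rising sequence and is exposed in the same way.

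The study is meant to inform the regimen of a later efficacy and safety study, so a misread tolerability profile would carry forward.

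**Working it through.** The protocol gives no figure of its own to reproduce on this point. The sample size of 8 in section 5.4 is set by analogy with earlier studies. The steps below size the exposure.

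**Inputs from the protocol:** 8 patients (5.4); 4 dosing visits each, so 8 × 4 = 32 visits; 3 × 7 = 21 days from visit 3 to visit 6 (Table 2); at least 2 exacerbations in the previous year (12.1.g).

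**Assumptions:** the rate is constant, patients are independent, and the 12.1.g count carries forward as a rate. Rates of 1, 3 and 4 per year are shown for range. Episode lengths of 7, 14 and 21 days are assumed, as the protocol gives none.

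**Step 1: an onset during the dosing period.** Per patient, p = 1 − exp(−rate × 21/365). For at least one of 8, P = 1 − (1 − p)^8.

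| Rate per year | p per patient | Expected of 8 | At least one of 8 |
|---|---|---|---|
| 1 | 5.6% | 0.45 | 37% |
| 2 | 10.9% | 0.87 | 60% |
| 3 | 15.9% | 1.27 | 75% |
| 4 | 20.6% | 1.64 | 84% |

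At 2 per year the exponent is 2 × 21/365 = 0.115, so p = 1 − exp(−0.115) = 10.9% and P = 1 − 0.891^8 = 60%. The chance of at least two affected patients is 21%.

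**Step 2: a dosing visit that falls inside an episode.** This bears more directly on a per-dose proportion. The share of visits in an episode is q = rate × length/365. For a given dose level, P = 1 − (1 − q)^8. At 2 per year:

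| Assumed length | q | Expected of 32 visits | Given dose level has at least one |
|---|---|---|---|
| 7 days | 3.8% | 1.2 | 27% |
| 14 days | 7.7% | 2.5 | 47% |
| 21 days | 11.5% | 3.7 | 62% |

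**Step 3: weight of one patient.** 1/8 = 12.5 percentage points. An observed 1 of 8 has an exact 95% interval of 0.3% to 52.7%.

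**Step 4: which endpoints are exposed.**
- *Symptom counts:* exposed. There is no pre-dose score, and events count whatever their cause.
- *Baseline-to-end comparison (9.2):* exposed. It has no same-day anchor.
- *Acute FEV1 drop:* largely protected, because each inhalation has its own pre-dose spirometry (7.3.7). However, 7.1.1 and 9.1 do not name that value as the reference.
- *AUC:* no figure in the protocol links an exacerbation to deposition or exposure.

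**The case against.** A reader might infer that all tolerability and PK results are confounded with the course of the disease. The documents do not support that. A change in airway state between visits shifts the pre-dose FEV1 and need not produce a post-dose drop. For AUC there is no effect size to work from, the nominal dose spans eightfold, and drug left in the device and inspiratory flow are both measured. These points stand, and the concern does not extend to either endpoint.

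A reader might also infer that the plan attributes every such symptom to the dose. It does not. Withdrawal for cough or dyspnoea under 7.4.1 requires a direct link to the inhalation, a medical check precedes dosing, and 9.2 calculates differences without assigning a cause. The co-medication list will also keep out some patients under treatment for infection. So symptoms *can* be misread, not that they *are*. But the withdrawal rule does not govern the 9.1 count, and the co-medication list misses an untreated exacerbation or one treated with an unlisted antibiotic.

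The 60% should not be taken as the chance that a per-dose result is distorted. It counts onsets over 21 days, and it rests on a prior-year count that 5.2 does not impose. Even a visit within an episode moves the proportion only if that patient would not otherwise have reported an event.

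Finally, rising order is a deliberate safety choice in a descriptive pilot study. That is a fair reason to keep it, and nothing here asks for it to change. It does make disease stability the condition on which the comparison across doses depends.

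**Conclusion.** The point holds for symptom adverse events and for the 9.2 comparison. The protocol sets no requirement for stable disease, its two descriptions of the population disagree, and its symptom counts cannot separate an exacerbation from the dose given that day.

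If 2 exacerbations per year continues at a constant rate, at least one onset among 8 patients during dosing is more likely than not: about 60%, with 37% at 1 per year and 75% at 3 per year. A given dose level includes a patient in an episode with a chance of about 27% to 62% for assumed lengths of 7 to 21 days. Each such patient can shift that level's proportion by up to 12.5 points. The onset figures leave out patients already in an episode, or recovering from one, at entry. No different sample size follows from this. It should be corrected because eligibility and what is recorded at each visit are fixed by the protocol and cannot be repaired at analysis.

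**What to change.** 1. **Eligibility.** Add to 5.2 a requirement of clinically stable disease before visit 3, with the period set by the sponsor, and reconcile 5.2 with 12.1.g on exacerbation history.
2. **Record.** At each dosing visit, note pre-dose cough and dyspnoea, exacerbation status and any new antibiotic. Item 1 alone is not enough: at 2 per year, the chance of at least one onset among 8 in any single 7-day step is still about 26%.
3. **Counting rule.** Keep recording all events, but count as dose-related those symptoms that are new or worse than the same day's pre-dose record.
4. **FEV1 reference.** Name the same-visit pre-dose value in 7.1.1 and 9.1 as the reference for the drop of more than 10%.
5. **Summaries.** Make per-dose tolerability over all visits the main summary, and show it without exacerbation visits as a sensitivity summary. Dropping those visits outright could hide real intolerability, since the protocol itself reports more dyspnoea and wheezing on inhaled tobramycin than on placebo.
6. **Schedule.** The sponsor should state how the fixed 7-day steps in Table 2 apply when an exacerbation occurs between visits. The clinical handling is the sponsor's decision.

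The cost is slightly slower recruitment, one extra case report form item per dosing visit and a few lines of text.

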### 5.3 Exclusion criteria

- Pregnant or breast feeding
- Subjects with known or suspected renal, auditory, vestibular or neuromuscular dysfunction, or with severe, active haemoptysis,
- History of adverse events on previous tobramycin or other aminoglycoside use
- No concurrent use of cyclosporin, cisplatin, amfotericin B, cephalosporins, polymyxins, vancomycin and NSAIDs.

### 5.4 Sample size calculation

We assume to need eight participants for this study. A specific calculation of the number of subjects needed is difficult, but low numbers have provided good results in other dry powder inhalation studies of antibiotics: A single dose study with dry powder inhalation of colistin for cystic fibrosis (CF) patients by LeBrun et al was performed with 5 patients. Another single dose study with dry powder colistin inhalation by Westerman et al was performed with 10 CF patients. Geller et al performed a single dose with a dose escalation study of dry powder tobramycin inhalation with 12 CF patients in each dose escalation arm. Each arm inhaled a fixed dose. Newhouse et al did a 5 period study with technetium labeled dry powder tobramycin with 14 healthy volunteers. First 3 periods were single dose. The last period was a 6-fold dose. Pilcer et al performed a single dose study with dry powder tobramycin inhalation in 9 CF patients. Therefore, we expect the 8 subjects in our single ascending dose study to be sufficient.

## 6. INVESTIGATIONAL PRODUCT

### 6.1 Name and description of investigational product(s)

Dry powder (DP) tobramycin consists of pure spray dried tobramycin free base. It is a white to off-white, hygroscopic powder with a particle size distribution appropriate for pulmonary administration. One dose of 30 mg tobramycin is sealed in an aluminium blister. Coarse crystalline  $\alpha$ -lactose monohydrate particles are added to the blister (not blended with the tobramycin) to break up any agglomerate that forms during storage.

### 6.2 Summary of findings from non-clinical studies

Preclinical data show that target organs for tobramycin toxicity are the kidneys and the vestibular/cochlear functions. This toxicity was shown at systemic tobramycin levels that were higher than can be achieved by inhalation of the recommended clinical dose given by nebulisation (Summary of Product Characteristics (SPC) TOBI®, SPC Bramitob®).

Administration of inhaled tobramycin during up to 28 consecutive days might give rise to modest and unspecific signs of irritation of the respiratory tract, that were fully reversible on therapy discontinuation (SPC Bramitob®).

Subcutaneous administration at doses of 100 mg/kg/day in rats and 20 mg/kg/day in rabbits were not teratogenic during organogenesis. Higher parenteral doses induced maternal toxicity and abortion in rabbits and were not relevant to be assessed on teratogenicity (SPC TOBI®, SPC Bramitob®).

No genotoxicity was shown for tobramycin (SPC Bramitob®).

### 6.3 Summary of findings from clinical studies

Several studies in the CF population with inhaled tobramycin were done in the late eighties and early nineties of the last century with promising results. However not all therapies that are effective in CF are effective in non-CF bronchiectasis.

Later, studies with tobramycin solution for inhalation were performed in patients with non-CF bronchiectasis. Barker et al investigated 74 patients divided in 2 groups. 37 patients received 300 mg tobramycin solution via a nebulizer twice daily for 28 days, the others received placebo. The patients treated with tobramycin had a significant reduction in sputum *P. aeruginosa* density at all time points of the study. The placebo group had a negligible change in sputum density at all time points. Unfortunately, the incidence of dyspnoea, chest pain and wheezing was significantly greater in the tobramycin group. Orriols et al studied 17 patients with non-CF bronchiectasis colonised with *P. aeruginosa*, divided in 2 groups. Group A received both tobramycin and ceftazidim via nebulisation inhalation and group B was treated symptomatically. One patient in group A withdrew due

to bronchospasm despite intense bronchodilator treatment. One patient in group B died due to respiratory failure after 300 days of follow up. No differences in lung function or arterial blood gas analysis were seen between the two groups. There was only one hospital admission in group A and 7 patients who had to be admitted in group B. In both groups *P. aeruginosa* was still present. They did not study sputum density .

Couch et al studied 74 patients with non-CF bronchiectasis colonized with *P. aeruginosa*. Patients were evenly divided in two groups, one group is receiving tobramycin inhalation therapy and the other group receives placebo. The treatment group received tobramycin for 4 weeks 300 mg twice daily. This group had a significant reduction in sputum *P. aeruginosa* density while the placebo group showed no change. The incidence of dyspnoea, wheezing and chest tightness was again significantly greater in the tobramycin group .

## **6.4 Summary of known and potential risks and benefits**

### **6.4.1. Risks (SPC TOBI®, SPC Bramitob®)**

Tobramycin, as all aminoglycosides, should be used cautiously in patients with known or suspected renal, auditory, vestibular or neuromuscular dysfunction, or with severe, active haemoptysis. Serum concentrations of tobramycin should be monitored through venipuncture. Parenteral aminoglycosides have been associated with hypersensitivity, ototoxicity and nephrotoxicity. No evidence of nephrotoxicity or of ototoxicity was shown during clinical trials with inhaled tobramycin.

Patients with neuromuscular disorders or other conditions characterized by myasthenia, should receive therapy with inhaled tobramycin with great caution because tobramycin might aggravate muscle weakness.

Bronchospasm has been reported with nebulised tobramycin. Furthermore, inhalation of medicinal products might evoke a cough reflex, that has been shown to occur in treatment with both nebulised tobramycin as with Tobramycin Inhalation Powder . Cough might induce further haemorrhage in patients with active haemoptysis.

In controlled clinical trials with TOBI®, dysphonia and tinnitus were the only unwanted effects reported in significantly more patients treated with TOBI®. In controlled clinical trials with Bramitob, most common adverse events were those concerning the respiratory tract (cough, dyspnoea, increased expectoration, FEV1 reduction). Furthermore, nausea is reported as common adverse event (occurrence >1/100).

